### Analysis plan

2.8

Baseline characteristics will be compared among the two arms of the study. This would ensure the identification of any chance imbalances despite randomization. Intention-to-treat analysis will be considered. At each follow-up point, a comparison between groups will be made. Student's *t*-tests will be used to compare the means for continuous variables (upon checking of assumptions), and confidence intervals for mean differences will be provided. For dichotomous outcomes (other than mortality), the *Z*-test for comparison of proportions will be computed along with 95% confidence intervals for the difference of proportions. To compare mortality between groups, the mortality rate ratio will be computed with 95% confidence intervals.

In case of imbalances in baseline characteristics, a multiple linear regression model will be fitted for continuous outcomes, multiple logistic regression for dichotomous outcomes, and Poisson regression (or Negative binomial) for mortality.

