**Methods and analysis:**

A 2 parallel-arm, multi-center randomized clinical superiority trial will be conducted with blinded outcome assessment. 152 HF patients (NYHA class II or III) will be recruited consecutively, and randomly assigned using permuted blocks; allocation will be concealed. The 12-week intervention will include evaluation, medical and nurse management, aerobic interval training, resistance exercise training, psychosocial support, and education. These will initially be delivered in a center, transitioning to home in 4 stages. Controls will receive similar management, but face-to-face continuous aerobic exercise sessions and resistance exercises. The main outcomes are cardiorespiratory fitness (VO_2_ max), functional capacity (m from 6 MWT), and quality of life (Minnesota Living with Heart Failure Questionnaire). Program adherence and completion, NT-proBNP, functioning, all-cause and HF-specific mortality and hospitalization, muscle strength, adverse events and cost will be secondary outcomes. These will be measured at baseline, end of intervention, and 12-month follow-up. The sample size was calculated considering 90% power, a significance level of 5%, a between-group difference equivalent to 1/2 MET, and a 10% potential loss to follow-up. Intention-to-treat analysis will be considered. Between-group differences will be assessed using Student's *t*-tests or *Z*-tests along with 95% confidence intervals, and the rate ratio will be computed to compare mortality.

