### Sample size

2.3

One hundred and thirty-eight patients (69 per group) are required to have a 90% chance of detecting as significant at the 5% level, a difference in the primary outcome measure of maximum cardiorespiratory capacity (VO_2_ max), assuming 15 ml/Kg/min in the control group and 16.75 ml/Kg/min in the experimental group at intervention end. The VO_2_ max assumed in the control group is that achieved by the experimental group with exercise-based CR in the HF-ACTION trial (9), with a standard deviation of 3.15 calculated with the range rule. The VO_2_ max in the experimental group was assumed with an intermediate minimal important difference of 1/2 MET (1.75 ml/kg/min) (30, 31). If a potential 10% loss of follow-up is added, results in 152 patients (76 per group). Sample sizes were also calculated for the other two primary outcomes, functional capacity, and HRQoL, with fewer patients needed to test the underlying hypothesis.

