–Program adherence and completion. For face-to-face activities, program adherence is defined as the percentage of total prescribed sessions completed. For home-based activities, the percentage of activities carried out at home of the prescribed ones will be computed, based on patient recordings in a diary. Program completion is considered as “yes” where participants attended most of the sessions and components of the CR intervention, and underwent a formal reassessment by the CR team at the end of the program (54).–Pro-B-type Natriuretic Peptide (BNP), as a biomarker with prognostic utility. When it is higher than 1,000 pg/ml, there is a higher probability of having events such as hospitalizations (55, 56). The determinations will be carried out in duplicate from serum samples by the fluorescence immunoassay technique in the laboratory of one of the participating centers (Hospital Clínico de la Universidad de Chile).–Functioning defined as the ability to perform basic, instrumental and advanced activities of daily living. It will be measured with the Activities of Daily Living Questionnaire—Technology (ADLQ-T). This instrument evaluates 7 areas related to self-care (6 items), home care and management (6 items), work and recreation (4 items), shopping and money (3 items), travel and transfers (3), communication (5 items) and technology (5). Each item is scored from 0 to 3, where 0 is no problem for the activity and 3 indicates that the activity cannot be performed. Additionally, when an aspect is part of the activities of the patient, it is scored 9. The ADLQ-T has been validated and proven useful in the Chilean population (57, 58).–Mortality and hospital admission will be measured separately and as a composite outcome. All-cause and HF-specific mortality and hospitalization will be differentiated. Death occurrence will be monitored by study personnel through a review of a public registry. The death certificate and any associated medical documentation will be copied for consideration by the adjudicating committee. Hospitalization occurrence will be assessed by study personnel through chart review at each participating center and supplemented by phone calls to participants every two months, using a standardized script. When the participant reports a hospitalization, all associated documents (i.e., tests and exam reports) will be collected from clinical charts at each center. A central adjudication committee will review all materials. This committee will be composed of three clinician-scientists (at least one will be a cardiology specialist) who will make the final decision about the event and specify the final death cause and hospitalization diagnosis with the corresponding ICD-10 code.–Upper and lower-body muscle strength will be assessed through grip strength and the chair stand test, respectively. Grip strength will be performed with a Jamar® Plus + electronic handheld dynamometer (Patterson Medical, Cedarburg, WI, USA) with the participant seated. Three attempts will be made on each hand alternately with 30 s of rest. The highest value of the 6 attempts will be reported (59). The chair stand test will be performed with the participant in a seated position in a chair without armrests and without wheels, feet flat on the floor, and arms crossed on the chest. From this position, they will be directed to rise fully and return to the starting position as many times as possible over 30 s. The number of repetitions achieved will be recorded (60).–Cost will be assessed through micro-costing from the perspective of health care system. A cost pool will be constructed for each CR program. The direct cost of labor (professional and administrative), depreciation of equipment and instruments, and the goods and services of normal consumption will be included. Indirect costs will also be considered, obtained from the calculation of indirect structural costs as an average percentage of direct costs in each center. Building depreciation costs will be discounted at a factor of 0.02, a rate obtained from a previous study performed by the Chilean Ministry of Health that included all public hospitals (61). In addition, out-of-pocket spending by patients will be costed (62), as too many patients are paying out-of-pocket for CR (63) and this impacts adherence.–Exercise-related adverse events: adverse events during exercise, such as myocardial ischemia or malignant arrhythmias, and serious adverse events, such as a death in the exercise sessions, will be reported to the corresponding ethics committee. All events will be registered for the final analysis.All outcomes will be measured at baseline, at 3 months (equivalent to stage three in the experimental group and at the end of the program in the control group), and at 12 months of follow-up from recruitment. The personnel assessing outcomes will be blinded to intervention assignment. In Table 4, all outcomes, their measurement, and assessment schedules are presented.

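### Natriuretic peptide is by default compared without its baseline value and with no log scale named; prespecified log-scale regression on baseline would recover power at no extra data cost

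*Protocol article*

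**What the plan says.** Section 2.8 gives one default for continuous outcomes at each follow-up: Student's t-tests "will be used to compare the means for continuous variables (upon checking of assumptions), and confidence intervals for mean differences will be provided". The abstract repeats it: "Between-group differences will be assessed using Student's" t-tests or Z-tests, with 95% confidence intervals. The second paragraph of section 2.8 adds multiple linear regression for continuous outcomes, but only where baseline characteristics turn out to be imbalanced.

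Section 2.7 lists natriuretic peptide as a secondary outcome on the pg/ml scale and gives its prognostic meaning: "When it is higher than 1,000 pg/ml, there is a higher probability of having events such as hospitalizations". The same section and Table 4 schedule it at baseline, 3 months and 1 year. The article gives no standard deviation, expected effect or baseline correlation for it. The only sample size shown with its inputs is for VO2 max in section 2.3.

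**The concern.** Two features of the default fit this marker poorly.

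First, the baseline value is left out of the comparison unless chance imbalance is observed. Baseline adjustment is worthwhile mainly because the baseline value predicts the follow-up value. That holds whether or not the arms happen to differ at entry, so observed imbalance is the wrong trigger.

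Second, the named summary is a difference in means, and no log scale is mentioned. A natriuretic peptide is positive and plausibly has a long right tail in this population. Table 1 admits ejection fractions from 40% or less to 50% or more, NYHA class II and III, glomerular filtration down to 20 ml/min, and atrial fibrillation with a resting rate up to 90. On the pg/ml scale a few very high values would inflate the variance.

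At stake is the chance of detecting a real peptide difference in a trial sized for another outcome.

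**Working it through.** **The plan's own figure.** Section 2.3 states that "One hundred and thirty-eight patients (69 per group) are required", with 90% power at the 5% level, "assuming 15 ml/Kg/min in the control group and 16.75 ml/Kg/min in the experimental group at intervention end", and "with a standard deviation of 3.15 calculated with the range rule". The two-sided formula gives n per arm = 2(1.960 + 1.282)² × 3.15² / 1.75² = 2 × 10.51 × 3.24 = 68.1, rounded up to 69, so 138 in all. The figure reproduces. Sidedness is not stated; one-sided testing would give 56 per arm. I use 69 per arm and two-sided 5% below.

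**Assumed inputs for the peptide (none is in the documents).** Log-normal values; log-SD σ of 0.8, 1.0 or 1.2; log-scale baseline-to-follow-up correlation ρ of 0.5, 0.7 or 0.8; true geometric mean ratio 0.70, so δ = ln 0.70 = −0.357.

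**Method.** 10,000 simulated trials per scenario (Monte Carlo error at most 0.5 points), comparing four analyses of the follow-up value. ANCOVA here means linear regression on arm with the baseline value as covariate. Power in percent at ratio 0.70:

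| σ | ρ | raw t-test | log t-test | raw ANCOVA | log ANCOVA |
|---|---|---|---|---|---|
| 0.8 | 0.5 | 61.0 | 74.4 | 70.1 | 85.4 |
| 0.8 | 0.7 | 61.7 | 74.3 | 82.4 | 95.2 |
| 0.8 | 0.8 | 61.1 | 73.8 | 91.7 | 99.1 |
| 1.0 | 0.5 | 38.9 | 54.9 | 44.6 | 66.6 |
| 1.0 | 0.7 | 38.6 | 55.3 | 55.9 | 82.4 |
| 1.0 | 0.8 | 38.6 | 54.7 | 67.5 | 93.1 |
| 1.2 | 0.5 | 24.2 | 40.8 | 27.9 | 50.9 |
| 1.2 | 0.7 | 24.3 | 40.5 | 34.8 | 67.3 |
| 1.2 | 0.8 | 24.6 | 41.9 | 44.9 | 81.9 |

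**Cross-check by formula.** Log ANCOVA has residual SD σ√(1 − ρ²), so power ≈ Φ(|δ| / [σ√(1 − ρ²) × √(2/n)] − 1.96). With σ = 1.0, ρ = 0.7 and n = 69, the residual SD is 0.714, the standard error is 0.714 × 0.170 = 0.122, and power is Φ(2.93 − 1.96) = 83.5%. The simulation gave 82.4%. Setting ρ = 0 gives 55.4% for the log t-test, against 55.3% simulated.

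**Splitting the gain.**
- Raw t-test to log t-test: from 12.6 points (61.7 to 74.3) to 17.3 points (24.6 to 41.9).
- Log t-test to log ANCOVA: from 10.1 points (40.8 to 50.9) to 40.0 points (41.9 to 81.9).
- Both together: from 24.4 points (61.0 to 85.4) to 57.3 points (24.6 to 81.9).
- Adjustment without a log scale also helps. In the central case (σ = 1.0, ρ = 0.7) it raises power from 38.6% to 55.9%.

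**Other effect sizes.** At ratio 0.80 the raw t-test has 11% to 29% and log ANCOVA 23% to 77%. At ratio 0.65 the ranges are 33% to 78% and 67% to 99.9%. The direction is the same in every scenario.

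**Validity.** With no true effect, the raw t-test rejects in 4.0% to 5.0% of trials and log ANCOVA in 4.7% to 5.2%. The t-test is not invalid here.

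**The case against.** The strongest reply is that the article does not commit to a raw-scale t-test for the peptide. The t-test is conditional on an assumption check, which a strongly skewed marker might well fail, and a transformation could be set out in a statistical analysis plan that is not shown. This stands. A reader might infer that the peptide will be tested on untransformed means come what may, but the text does not say so. The raw t-test column therefore shows the default if it is carried through, not a fixed plan. The absence of transformation detail alone would not be a finding in a condensed article.

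Other inferences also go too far:
- That the t-test is the only method named for continuous outcomes: linear regression is named too, conditionally.
- That the scale will be chosen on unblinded data: section 2.8 does not say who makes the check, when, or on which data.
- That the peptide carries the trial's link to mortality and admissions: the Discussion gives that role first to exercise capacity and presents the peptide as an addition, and section 2.7 measures deaths and admissions directly.

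It is also fair to say that a 30% reduction against an active exercise comparator has no support in the documents, and that the power figures are wholly assumed.

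The adjustment rule survives all this. It is stated in the text: regression depends on observed imbalance. Even an analysis plan that added a log transformation would leave the baseline value unused by default if it kept that rule.

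**Conclusion.** The point holds as an inexpensive improvement, not as an error. The stated default for continuous outcomes is an unadjusted comparison of follow-up means, with regression reserved for observed imbalance, even though a baseline peptide value is planned for every patient. Under the assumed range at a ratio of 0.70, prespecified log-scale adjustment would add about 24 to 57 points of power over an untransformed t-test. If the assumption check led to a log-scale t-test instead, the remaining gain from baseline adjustment would be about 10 to 40 points. The direction is robust across the scenarios. The size depends on skewness, correlation and effect, none of which the documents give. Type I error, the primary outcomes and the stated sample size are unaffected by this point.

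**What to change.** In section 2.8, or in the statistical analysis plan as an explicit departure from the published default, prespecify that at each follow-up log natriuretic peptide is analyzed by linear regression on arm with log baseline peptide as covariate, regardless of observed baseline imbalance. Report the arm effect as a ratio of geometric means with a 95% CI.

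This takes about two sentences and needs no extra samples, visits or patients. The one downside is that the effect is read as a percent difference instead of a difference in pg/ml; descriptive summaries in pg/ml by arm and visit can stand beside it.

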### Design

2.1

A pragmatic, multi-center, 2-parallel arm randomized clinical trial with blinded outcome assessment will be conducted. In this study, a hypothesis of superiority is tested (i.e., a comprehensive and hybrid CR program produces better results than a conventional exercise-based supervised program). This trial will be pragmatic in that it examines the outcomes of the experimental intervention compared with a control group under circumstances that closely approximate the real world, in a low-resource setting. Patients will be recruited in 4 health centers in Chile. It is not possible to double-blind in a CR trial, but personnel undertaking outcome assessment will be blinded to group allocation. Finally, the randomization process (concealed allocation 1:1) will allow balancing in both groups of all known and unknown sociodemographic and clinical characteristics that could confound the association between the intervention and results.

The trial protocol is registered in clinicaltrials.gov (number NCT06313684). It will be reported in accordance with the CONSORT statement (25), including the extensions for non-pharmacologic treatment interventions, and pragmatic trials. A diagram of the trial showing activities in detail is presented in Figure 2.

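### The main analysis of continuous outcomes ignores the measured baseline value, and adjustment is added only if an undefined baseline imbalance is seen

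*Protocol article*

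**What the plan says.** The Analysis plan (section 2.8) calls for a between-group comparison at each follow-up point. For continuous outcomes, Student's t-tests "will be used to compare the means for continuous variables (upon checking of assumptions"), with confidence intervals for mean differences. Dichotomous outcomes other than mortality get a Z-test and a difference of proportions, and mortality gets a rate ratio. The abstract names the same tests and sets no condition on them.

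The arms are also compared at baseline, with the declared purpose of finding chance imbalances. Adjustment depends on what that comparison shows: "In case of imbalances in baseline characteristics, a multiple linear regression model will be fitted for continuous outcomes, multiple logistic regression for dichotomous outcomes", with Poisson or negative binomial regression for mortality.

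The outcomes section (2.7) states: "All outcomes will be measured at baseline, at 3 months", and then at 12 months. Table 4 marks a baseline measurement for all three primary outcomes (cardiorespiratory fitness, 6MWT, health-related quality of life) and for natriuretic peptide and muscle strength.

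The Sample size section (2.3) works on raw end-of-intervention values, "assuming 15 ml/Kg/min in the control group and 16.75 ml/Kg/min in the experimental group at intervention end", "with a standard deviation of 3.15 calculated with the range rule", and uses no baseline correlation.

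**The concern.** Three things are at stake.

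- **Precision.** A patient's VO2max, walking distance or MLHFQ score at 3 months is likely to be related to the same measure at baseline. A t-test on follow-up values leaves that explainable variation in the error term, although the trial has already paid to measure it.
- **Imbalance that is not declared.** A moderate chance difference in baseline VO2max carries into the unadjusted follow-up difference unless someone calls it an imbalance. Fixed adjustment removes it without anyone having to decide.
- **An open choice.** The trigger is read from the trial's own data and has no criterion. Once it fires, an unadjusted and an adjusted result can both exist, and neither is named as primary. For dichotomous secondary outcomes, moving from a difference in proportions to logistic regression may change the effect measure as well.

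**Working it through.** **Inputs from the document.** Difference 16.75 − 15 = 1.75 ml/kg/min; SD 3.15; 5% level; 90% power; 1:1 allocation; 10% loss; 76 randomised per arm. Sidedness is not stated. Two-sided is inferred because it reproduces the plan's number and one-sided does not (56 per arm).

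**Assumption.** The correlation r between baseline and follow-up values is not in the document. I show 0.3, 0.5 and 0.7, and 0.8 in places.

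**1. The plan's own figure.** n per arm = 2 × (1.960 + 1.282)² × (3.15/1.75)² = 68.09, rounded up to 69, so 138 in total. This matches exactly as an unadjusted two-sample comparison of follow-up means. Power at 69 per arm is 90.4% by the normal approximation and 90.0% by the noncentral t. With 10% loss, 76 × 0.9 = 68.4, so about 68 completers per arm and 89.5% power.

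**2. Gain from always adjusting.** Adjustment for the outcome's baseline value multiplies the residual SD, and so the width of the confidence interval, by √(1 − r²). The standardised effect becomes (1.75/3.15)/√(1 − r²) = 0.5556/√(1 − r²).

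| r (assumed) | √(1 − r²) | CI narrower by | Power, 68 per arm |
|---|---|---|---|
| 0 (t-test) | 1.000 | – | 89.5% |
| 0.3 | 0.954 | 5% | 92.1% |
| 0.5 | 0.866 | 13% | 96.0% |
| 0.7 | 0.714 | 29% | 99.5% |

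**3. Does the conditional rule recover the gain?** This was simulated with 69 per arm and 200,000 trials per setting. The rule was taken as: adjust if the baseline value differs at p < 0.05, otherwise use the t-test. That threshold is an assumption, since the plan gives none.

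| r | Power, conditional rule | Power, always adjusted |
|---|---|---|
| 0.3 | 90.3% | 92.3% |
| 0.5 | 90.8% | 96.2% |
| 0.7 | 91.7% | 99.5% |

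Most of the gain is lost because the rule seldom adjusts.

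**4. Type I error.** The same simulation with no treatment effect:

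| r | t-test, overall | Mechanical conditional rule | Smaller p-value of the two analyses | t-test, given baseline imbalance at p < 0.05 | Adjusted, given the same imbalance |
|---|---|---|---|---|---|
| 0.3 | 4.9% | 4.7% | 6.3% | 9.3% | 4.7% |
| 0.5 | 5.0% | 4.3% | 7.3% | 18.5% | 4.9% |
| 0.7 | 5.0% | 3.6% | 8.3% | 33.3% | 5.1% |

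The mechanical rule is conservative. Inflation needs a free choice between the two results.

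**5. Imbalance that would probably not be declared.** Take a baseline VO2max difference of 1.5 standard errors (p about 0.13). With the same SD at baseline (an assumption), the standard error is 3.15 × √(2/69) = 0.536. The unadjusted follow-up difference then shifts by 1.5 × 0.536 × r:

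- r = 0.3: 0.24 ml/kg/min, or 14% of the 1.75 target.
- r = 0.5: 0.40 ml/kg/min, or 23%.
- r = 0.7: 0.56 ml/kg/min, or 32%.

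**The case against.** The strongest reply is that nothing here is invalid. A t-test in a randomised trial is unbiased over randomisations. It matches the basis of the sample size, and the trial has about its stated 90% power under the stated analysis. The gain depends on a correlation that the document does not give. At r = 0.3 it is small, and at 12 months r may well be lower than at 3 months. All of this stands, and it limits the point to precision and pre-specification. It does not remove the point: the rule is written into the plan, it recovers little of the available precision, and changing it costs almost nothing.

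A reader might also infer several stronger claims that the document does not support.

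- **That the regression replaces the t-test.** The text says only that a model will be fitted. It may replace or accompany the t-test. What can be said is that the primary result is not identified once the trigger fires.
- **That the rule inflates type I error.** Applied mechanically, it does not (step 4). The 7-8% arises only if the better result may be chosen, and the plan does not license that.
- **That the effect measure of the primary outcomes can change.** All three are continuous, and both the t-test and linear regression estimate a mean difference. Mortality stays on a rate-ratio scale. Only dichotomous secondary outcomes are exposed, and the plan does not say that an odds ratio would be reported.
- **That the trigger is close to a coin toss.** With 10 to 20 independent characteristics each tested at p < 0.05, the chance of at least one hit is 1 − 0.95¹⁰ = 40% to 1 − 0.95²⁰ = 64%. The plan states neither the number nor the threshold, and heart failure measures are unlikely to be independent. With 5 characteristics the figure is already down to 23%.
- **That centre and a covariate list are wrongly missing.** The article is silent on both. Such detail commonly sits in a statistical analysis plan, so its absence is no error.

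**Conclusion.** The concern holds as a question of efficiency and pre-specification, not of validity. Section 2.8 makes the unadjusted comparison the main analysis although the baseline value of each primary outcome is measured. It ties adjustment to an undefined imbalance and does not say which result is then primary.

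The size depends on the assumed r. The gain is modest at 0.3 and substantial at 0.5 to 0.7. If baseline VO2max happens to be clearly imbalanced, the unadjusted test is misleading for that particular trial: its conditional type I error is roughly 18-33% at r = 0.5-0.7, against about 5% with adjustment. The results in steps 2 to 4 assume normal data and a common linear relation between baseline and follow-up in both arms.

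The change should be made. The trial would remain interpretable without it.

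**What to change.** In section 2.8, before outcome data are seen:

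1. Delete the imbalance trigger.
2. For each continuous outcome, pre-specify one linear model with arm and that outcome's baseline value as the main analysis at each follow-up point, whatever the observed imbalance.
3. Keep the unadjusted t-test as a sensitivity analysis, labelled as such.
4. For dichotomous outcomes, keep the difference in proportions as the effect measure whether or not the analysis is adjusted.

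A centre term and a mixed model over 3 and 12 months are optional and not needed to cure the defect.

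The cost is one paragraph of analysis wording, with no new data and no extra patients. The sample size can stay at 152, since the adjustment only adds to the power already planned.

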Another limitation will be the potential for contamination (i.e., that the participants in the control group participate in a comprehensive CR program). While this is a possibility given that it has been described in previous studies, in the context of this trial with an exercise-based CR control group as well as given CR in Chile is not highly comprehensive (65) and such that participants in one program would not participate in another subsequently within 9 months as there would be none proximately, it is very highly unlikely.

Finally, considering intermediate outcomes as primary outcomes, basically, maximum exercise capacity, may be an important limitation, especially for the findings to be a valid basis for potential clinical recommendations. Nevertheless, maximum exercise capacity is considered a valid predictor of such clinical events as death and hospital admission (66) and, for that reason, is the basis of our hypothesis. We have also integrated other primary outcomes, such as functional capacity as an indicator of functioning, a key outcome in CR, and HRQoL, which are equally relevant in this condition as a patient-reported outcome, and are useful for decision-making (67). Additionally, we have included the measurement of pro-BNP, a biomarker which is a good predictor of mortality and especially of hospitalization (55, 56). Likewise, and in the certainty that it is necessary to have information on the long-term impact of this type of intervention (with all its complexities), it has been planned to monitor the survival and hospitalizations of the participants beyond the 12-month follow-up.

We hypothesize that this tailored model of CR will result in greater adherence and completion of the program, resulting in improved cardiorespiratory fitness (a good predictor of mortality and hospitalization) and HRQoL in HF patients. If superiority is demonstrated, a pragmatic, hybrid (center and home-based) and comprehensive model of CR will be available for implementation in the healthcare system, especially in low and middle-income settings, to improve outcomes for the many HF patients in need.

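### By elimination, hospital admission and the death-or-admission composite are compared as simple proportions; first-event and rate analyses would use the data better, and negative binomial does not suit death

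*Protocol article*

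**What the plan says.** Section 2.7 (Outcomes, measures and follow-up assessments) lists the event outcomes as secondary: "Mortality and hospital admission will be measured separately and as a composite outcome". All-cause and HF-specific events are to be separated. Deaths come from a public registry. Admissions come from chart review at the participating centres, supplemented by calls to participants every two months. A central committee adjudicates both.

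Section 2.8 (Analysis plan) has three classes of outcome, compared at each follow-up point:

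- Continuous outcomes get t-tests.
- The second class opens with "For dichotomous outcomes (other than mortality), the" and goes on to a Z-test and a difference of proportions.
- Mortality gets a rate ratio with a 95% confidence interval.

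If baseline characteristics are imbalanced, the adjusted models are linear regression, logistic regression and, for the third class, "Poisson regression (or Negative binomial) for mortality".

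The section names neither hospital admission nor the composite. The Discussion adds that "it has been planned to monitor the survival and hospitalizations of the participants beyond the 12-month follow-up".

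**The concern.** Only mortality is excepted from the dichotomous class, so admission and the composite fall into it. Death happens once and is traced through a registry, yet it gets a rate-based analysis. Admission can recur and is found partly through contact with the patient, yet it is reduced to yes or no over a fixed denominator.

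Four things follow for admission as a proportion:

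- The time of the event is ignored.
- Second and later admissions are ignored.
- A patient lost early must be dropped or counted as event-free.
- A patient who dies before any admission counts as not admitted, so an arm with more early deaths can look better on admission.

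The first and third also apply to the composite; the last does not, because death is one of its components. For HF-specific events, death from another cause competes, and the section gives no way of handling this.

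For mortality the issue is narrow. Negative binomial regression models extra variation in repeat counts, and a patient contributes at most one death.

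**Working it through.** **1. Outcomes set against methods.**

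| Outcome (section 2.7) | Can recur? | Does death compete? | Method in section 2.8 |
|---|---|---|---|
| Death, all causes | No | No | Rate ratio; Poisson or negative binomial if imbalanced |
| Death, HF-specific | No | Other-cause death | As above |
| Admission | Yes | Yes | Z-test or logistic regression, by elimination |
| Death or admission, all causes | Not as a first event | No, death is a component | Z-test or logistic regression, by elimination |

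**2. The plan's own figure.** The Sample size section uses a difference of 16.75 − 15 = 1.75 ml/kg/min, an SD of 3.15, 90% power and a 5% level. Per arm, n = 2 × (1.960 + 1.282)² × 3.15² / 1.75² = 2 × 10.51 × 3.24 = 68.1, so 69 per arm and 138 in total. Then 138 × 1.10 = 151.8, so 152, or 76 per arm. The figure reproduces. It concerns VO2 max only: the document gives no event rate, event count or power for death, admission or the composite. All rates below are therefore assumptions.

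**3. Death: Poisson against Cox.** Simulated with 76 per arm, 12 months, 10% loss, control hazard 0.05, 0.10 or 0.20 per year, and ratio 1 or 0.6. The mean log rate ratio from Poisson with person-time and the mean log hazard ratio from Cox differed by at most 0.002. The ratio of standard errors was 1.00, and rejection rates agreed within 0.2 points (for example 20.8% for both at hazard 0.20 and ratio 0.6). Poisson with person-time is thus a sound model for death.

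**4. Admission: proportion against alternatives.** Simulated with 76 per arm, 12 months, control rate 0.4 or 0.8 admissions per year, gamma frailty with variance 1, death hazard 0.10 per year and 10% loss in each arm. Power is at a rate ratio of 0.6.

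| Control rate | Z-test, type I error | Z-test, power | Log-rank, first event, power | Event rate (robust), power |
|---|---|---|---|---|
| 0.4 | 5.2% | 22.5% | 23.2% | 30.2% |
| 0.8 | 5.5% | 32.7% | 34.0% | 48.0% |

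Gain from log-rank: 23.2 − 22.5 = 0.7 and 34.0 − 32.7 = 1.3 points. Gain from all admissions: 30.2 − 22.5 = 7.7 and 48.0 − 32.7 = 15.3 points.

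Type I error of the Z-test when the arms differ:

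- Loss of 5% versus 15%, lost patients counted as event-free: 5.5%.
- Loss of 0% versus 20%, counted the same way: 7.8%.
- Death hazard of 0.20 versus 0.10 per year: 6.0%.

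**5. How few deaths.** Assume 4% to 10% one-year mortality.

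- At 12 months, deaths per arm are 76 × 0.04 = 3.0 to 76 × 0.10 = 7.6. A large-sample 95% interval for the rate ratio multiplies and divides the estimate by exp(1.96 × √(2/d)), where d is deaths per arm. That is 4.9 at d = 3.0 and 2.7 at d = 7.6.
- At 3 months, with constant hazard, expected deaths per arm are 76 × (1 − 0.96^0.25) = 0.8 to 76 × (1 − 0.90^0.25) = 2.0. The chance that a given arm has none is 0.96^19 = 0.46 or 0.90^19 = 0.135 (76 × 0.25 = 19). The chance that at least one arm has none is 1 − (1 − 0.46)² = 0.71 or 1 − (1 − 0.135)² = 0.25. The ratio is then zero or undefined, and a large-sample interval fails.

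**The case against.** The strongest reply is that the assignment to a Z-test is an inference. Section 2.8 does not name admission or the composite, the dichotomous class has other clear members such as program completion, and a condensed article need not list a method for every secondary outcome. This stands in part. But the section does except mortality alone from that class, and no other stated class fits a yes/no admission or composite.

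Second, comparisons are made at fixed times, so follow-up is equal by design, and the Z-test roughly keeps its level when loss is small and equal. That stands, and it rules out calling the method invalid. The follow-up beyond 12 months appears only in the Discussion, with no analysis attached; a simple proportion would become a problem there only if its length varied between patients.

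Third, a reader might infer more than the document supports:

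- *That Poisson regression is wrong for death.* With log person-time as offset it is a constant-hazard model for a single event and the adjusted counterpart of the rate ratio that the plan names. The article does not state the offset, but an analysis plan may.
- *That the composite recurs and competes with death.* All-cause death is a component of it, and a first event happens once.
- *That about 15 of the 152 patients will lack event follow-up.* The 10% is an allowance in the VO2 max calculation. A patient who misses an exercise test can still be traced through the registry and charts.
- *That the wide mortality interval shows a wrong model.* It reflects few deaths and would be about as wide under Cox.

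**Conclusion.** The point holds as a matter of efficiency and robustness. Comparing admission and the composite as proportions is valid at a fixed 12 months with near-complete follow-up. It wastes event times and repeat admissions, and it is fragile to unequal loss or unequal death.

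Under the assumed rates, a first-event analysis gains only about 1 point of power; its main benefit is proper handling of censoring and competing death. The larger gain, about 8 to 15 points, comes from total admissions, which answer a different question. The distortion of type I error is small except under strongly unequal loss (7.8% at 0% versus 20%, with lost patients counted as event-free).

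Negative binomial has no proper use for death; the rest of the mortality analysis is sound. These are unpowered secondary outcomes, and the adjusted models apply only if baseline is imbalanced. This is a cheap improvement and does not threaten the trial's main conclusions.

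**What to change.** In section 2.8:

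- **First admission and the composite.** Analyse as time to first event by log-rank test and Cox regression, censored at last contact. Treat death as a competing event for admission alone, and other-cause death as a competing event for HF-specific outcomes: cause-specific hazards, with cumulative incidence curves that allow for the competing event. The all-cause composite needs no such step.
- **Total admissions.** Add a rate ratio from negative binomial regression with log follow-up time as offset, and state that it is a separate estimand from first admission.
- **Mortality.** Keep the person-time rate ratio, and Poisson regression with log person-time as offset for adjustment. Name an exact (conditional) interval for the rate ratio, because deaths will be few. Delete the negative binomial option.
- **Beyond 12 months.** State that the same methods apply to the extended follow-up.

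The cost is wording and slightly more analysis work on secondary outcomes. Event dates should be available from the death certificates and hospital documents already being collected. Sample size, visits and data collection do not change.
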